### Participants

Patients will be recruited from gastrointestinal endoscopy departments in 4 hospitals affiliated with Shanghai University of TCM, namely, Longhua Hospital, Yueyang Hospital of Integrated Traditional Chinese and Western Medicine, Shanghai Traditional Chinese Medicine-Integrated Hospital and Shanghai Municipal Hospital of Traditional Chinese Medicine.

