#### Inclusion criteria

Participants will be eligible if they meet all of the following criteria:1. Individuals aged from 18 to 75 years, regardless of gender2. Individuals who underwent complete painless endoscopic adenoma resection (excluding hot polypectomy, hot snare polypectomy and argon plasma coagulation) within 2 weeks before recruitment3. At least 1 but no more than 6 CRAs confirmed by histology (including tubular, tubulovillous, and villous adenoma)4. Boston Bowel Preparation Scale (BBPS) score ≥7 points5. The score of SDS in TCM ≥20 points6. Individuals with adequate organ function7. Individuals who provide informed consent and can cooperate with long-term follow-up

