### Outcomes

The primary outcome is the recurrence rate of CRA between the SJZD group and the placebo group at the first year after CRA removal. The number, size and location of adenomas will be recorded. Pathological type will also be recorded if recurrent adenomas meet the criteria for resection. Secondary outcomes include the following: 1) the recurrence rate of CRA at the second year post-polypectomy; 2) the pathological type of adenoma detected at either of the two endoscopies; and 3) the changes in spleen deficiency PRO scores after intervention.

Safety outcomes will comprise physical examinations, vital signs and laboratory examinations at every visit and AEs during the intervention phase. Laboratory indices will include routine blood tests, routine urine tests, routine stool tests, liver function tests, renal function tests and electrocardiograms. In the event of AEs, the onset time, symptoms and signs, duration of event and abnormal laboratory indicators or imaging results will be recorded. The definition and grade assessment of AEs are in accordance with the National Cancer Institute Common Terminology Criteria for Adverse Events (Version 5.0) (SERVICES USDOHAH, 2017).

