### Randomization and blinding

Permuted block randomization, which is stratified by recruiting sites, will be used to allocate participants to the SJZD group or placebo group in a 1:1 ratio by the SAS statistical analysis system. All drugs will be sealed in identical opaque envelopes only labeled with a random code number. Participants will be enrolled by clinicians and receive an envelope in sequence. An independent statistician will finish the randomization. Clinicians, nurses, researchers and patients who participate in this trial will all be blinded to the treatment assignment. The random number and treatment assignments will be sealed and reserved by the principal investigators of this study. The blinding will not be unmasked until the trial and data analysis finish or in the event of serious AEs. Emergency letters sealed in opaque envelopes will be sent to each recruiting site. Assignment information and emergent conditions are contained in the letter. If any serious AEs occur, the emergency letter will be opened, and the corresponding patient will be withdrawn from the trial. A report of serious AEs should be submitted to the principal investigators within 24 h. The codes of treatments will be uncovered after the closure of follow-up and the specific intervention relevant to the cords will be uncovered after data analysis.

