### Sample size

Based on a previous clinical trial, the effective rate of berberine, a famous Chinese medicine, in the prevention of CRA recurrence was 11% (Chen et al., 2020). The estimated effective rate of SJZD is 20% in this study. Following the 1:1 parallel control principle, SAS statistical analysis software was used to generate the sample size with a double-sided significance level of 0.05 and a power of 80% (α = 0.05, β = 0.2). Assuming that the dropout rate in each group was 10%, a requirement of 240 cases was determined (*n* = 120 in each group).

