### Statistical analysis

SAS statistical software will be used to analyze the data. The efficacy and safety of this study will be analyzed by the principle of intention-to-treat (ITT). The missing data will be filled by the method of the last observation carried forward. The measurement data will be expressed as the mean ± standard deviation or median (quartile interval) determined by whether the data are normally distributed and the variance is uniform. χ^2^ tests will be used to compare the primary and secondary endpoints between the SJZD group and the placebo group. The paired *t*-test and independent sample *t*-test will be used for intragroup comparison and intergroup comparison, respectively. Logistic regression analysis will be used for the factors affecting the recurrence rate. Interim analysis will be arranged when 50% of the sample is collected. Sub-group analyses will be determined based on characteristics of participants such as gender, body mass index or previous history of gastrointestinal diseases. *p* < 0.05 is considered statistically significant.

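### Allocation is stratified by four sites, but the named primary test is a plain chi-square; if sites differ it is mildly conservative, and a site-stratified test is a free, small improvement

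*Protocol article*

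**What the plan says.** The Randomization and blinding section sets the design: "Permuted block randomization, which is stratified by recruiting sites, will be used to allocate participants". The Participants section gives the number of strata: "Patients will be recruited from gastrointestinal endoscopy departments in 4 hospitals affiliated with Shanghai University of TCM".

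The Outcomes section defines a yes/no endpoint per patient: "The primary outcome is the recurrence rate of CRA between the SJZD group and the placebo group at the first year after CRA removal". Recurrence at the second year is a secondary outcome of the same kind.

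The Statistical analysis section then states that χ² "tests will be used to compare the primary and secondary endpoints between the SJZD group and the placebo group". It names no stratified test and no site term. The only regression model it mentions has another purpose: "Logistic regression analysis will be used for the factors affecting the recurrence rate". That sentence does not make the model the treatment comparison, and it does not list site.

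**The concern.** Blocking within hospital keeps the arms nearly equal in size in each hospital, so differences between hospitals largely cancel out of the treatment comparison. A chi-square on the pooled table does not know this. Its variance still includes the between-hospital component that the design has removed. If hospitals differ in recurrence or in detection, the standard error is therefore somewhat too large and the p-value somewhat too big.

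Some difference is plausible, because each site uses its own endoscopists and the Discussion lists endoscopic procedures among the influences on recurrence. What is at stake is a little power and the agreement between analysis and design.

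**Working it through.** **No stated figure to reproduce.** The article reports no number that depends on this choice. The check asks how far the two tests can differ.

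**Inputs from the article.** Four sites, 1:1 allocation, two-sided 0.05. There are 240 patients with 10% dropout, so 240 × 0.9 = 216 evaluable, or 108 per arm. The Sample size section gives rates of 11% and 20%.

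**Assumed inputs.** Equal site sizes (108 / 4 = 27 per arm per site), exact balance within site, the site-specific recurrence rates, and an 18-point absolute reduction in the first four scenarios. The article states none of these.

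**Direction.** Let p_s be the recurrence rate in site s under no treatment effect, and p̄ the mean over sites. With balance within sites, the variance of the arm difference is proportional to mean[p_s(1 − p_s)]. The pooled chi-square uses p̄(1 − p̄). The two differ by the between-site variance of p_s:

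p̄(1 − p̄) − mean[p_s(1 − p_s)] = mean[(p_s − p̄)²] ≥ 0

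So the ratio r = mean[p_s(1 − p_s)] / [p̄(1 − p̄)] never exceeds 1. The large-sample size of the nominal 5% test is 2 × [1 − Φ(1.96/√r)], which is at most 5%. The test can be conservative but, apart from discreteness, not anti-conservative.

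**Putting numbers in.**
- Sites 40, 43, 47, 50%: r = 0.24605 / 0.24750 = 0.994; size 4.9%.
- Sites 26.6, 35, 43.3, 51.6%: r = 0.2295 / 0.2382 = 0.964; size 4.6%.
- Sites 20, 35, 50, 65%: r = 0.21625 / 0.24438 = 0.885; size 3.7%.
- Sites 11, 17, 23, 29%: r = 0.1555 / 0.1600 = 0.972; size 4.7%.

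**Simulation at 27 per arm per site** (400,000 trials per cell, no continuity correction):

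| Assumed control rates by site | Reduction | Size, plain χ² | Size, CMH | Power, plain χ² | Power, CMH |
|---|---|---|---|---|---|
| 45% in all | 18 points | 4.8% | 4.8% | 79.7% | 79.4% |
| 40 to 50% | 18 points | 4.7% | 4.8% | 79.7% | 79.6% |
| 26.6 to 51.6% | 18 points | 4.5% | 5.1% | 83.7% | 84.6% |
| 20 to 65% | 18 points | 3.5% | 5.0% | 82.7% | 86.0% |
| 11 to 29% (mean 20%) | 9 points (mean 20% to 11%) | 4.8% | 5.0% | 45.4% | 46.2% |

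CMH gains nothing with no spread or a 10-point spread, about 1 point with 25 points and about 3 points with 45 points. On the article's own two rates, with the assumed 11 to 29% spread, it gains 0.8 points.

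**Sensitivity of the largest gain.** A constant 18-point reduction takes the 20% site down to 2%, which is extreme. Replacing it by a constant odds ratio of 0.40, which gives the same average reduction, yields power of 82.3% against 84.6%, a gain of 2.3 points.

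**The case against.** The strongest reply is that the text says only χ² tests. CMH is itself a χ² test, this is a condensed article, and an analysis plan that is not shown may specify the strata. That is fair as a caution. However, the article does name its primary test, and the usual meaning of an unqualified χ² comparison of two groups is the Pearson test on the pooled table. The point is about the method stated, not about a missing detail.

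The second reply is that the hospitals may hardly differ. All four are in Shanghai and affiliated with one university, experienced specialists follow one guideline, and entry requires a bowel preparation score of at least 7. This stands, and it is why the loss can be stated only conditionally. If hospitals do not differ, there is nothing to gain, and CMH gives up about 0.3 points of power.

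A reader might take the 26.6% to 51.6% in the Discussion as the spread to expect between sites. It is a range across published studies, which the Discussion links to a trend of higher recurrence with longer follow-up, so it serves here only as an illustration.

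A reader might also infer that the number of baseline adenomas should be adjusted for, since the Inclusion criteria admit "At least 1 but no more than 6 CRAs confirmed by histology". The article does not say how strongly that number predicts recurrence, and it neither lists nor excludes factors for its logistic regression. The documents do not support a finding there.

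**Conclusion.** The mismatch between the stratified allocation and the plain reading of the test is real, and its consequence is minor. If recurrence or detection differs between sites, the plain chi-square is conservative and loses roughly 1 point of power for a 25-point spread and 3 points for a 45-point spread. Otherwise it loses nothing. These sizes rest on assumed site rates, equal sites, 108 evaluable per arm and an 18-point effect that the article does not state.

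A reader might conclude that the primary p-value would be invalid or tilted towards the herbal treatment. It would not be: the error is in the cautious direction, so this is a matter of efficiency and consistency. Nor does it explain why power is near 45% on the article's 20% and 11%, when the Sample size section claims a calculation "with a double-sided significance level of 0.05 and a power of 80"%. Both tests give about that figure, so that gap belongs to the sample size and should be judged separately.

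**What to change.** In the Statistical analysis section, state that first-year recurrence will be compared by a CMH test stratified by the four recruiting sites, and reported with a site-stratified risk difference and its 95% confidence interval. Use the same method for year-2 recurrence. Keep the unstratified chi-square as a supportive analysis.

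The cost is one sentence. Site is known for every participant, so no new data are needed. The choice should be fixed before unblinding, so that the stratified and plain results cannot be chosen between afterwards.

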#### Endoscopic procedures

At every recruiting site, specialists with substantial experience will perform the endoscopic examinations and polypectomies. The clinical practice follows the guideline published by The Japanese Society of Gastroenterology (JSGE) (Tanaka et al., 2021). Adequate bowel cleaning will be required to ensure clear observation of the entire colorectum. All detected adenomas or polyps will be photographed, and standard endoscopic reports will be submitted by the endoscopists and preserved by the principal investigators. Tissue will be collected and stored following the routine clinical care and regulations of the Department of Pathology.

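### Randomisation is stratified by hospital but the recurrence comparison names a plain chi-square test with no site stratum; to the extent that recurrence differs between hospitals, that test is mildly conservative.

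*Protocol article*

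**What the plan says.** The section Randomization and blinding states: "Permuted block randomization, which is stratified by recruiting sites, will be used to allocate participants", with equal numbers in the two arms. Site is the only stratification factor named. Under Participants: "Patients will be recruited from gastrointestinal endoscopy departments in 4 hospitals affiliated with Shanghai University of TCM".

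The section Outcomes states: "The primary outcome is the recurrence rate of CRA between the SJZD group and the placebo group at the first year after CRA removal". This is a binary endpoint, repeated as a secondary endpoint at the second year.

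Under Statistical analysis, χ² "tests will be used to compare the primary and secondary endpoints between the SJZD group and the placebo group". The sentence mentions no stratum, no CMH statistic and no site term. The same section adds: "Logistic regression analysis will be used for the factors affecting the recurrence rate". That model is not presented as the treatment comparison, and its covariates are not listed.

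Under Endoscopic procedures: "At every recruiting site, specialists with substantial experience will perform the endoscopic examinations and polypectomies". So each hospital's own endoscopists find the lesions that make up the outcome. The article describes no central reading of the endoscopies.

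**The concern.** Balancing the arms within each hospital removes differences between hospitals from the treatment comparison. A chi-square test on one table for all hospitals does not know this. It estimates the variance as if the between-hospital differences were still random noise in the contrast. The estimated standard error is then larger than the true one, and the test rejects less often than its nominal level, both under the null and under a real effect.

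Site differences are plausible here because the outcome depends on what local endoscopists detect, and because the sponsor thought site important enough to stratify on. At stake is precision already built into the design but not used in the analysis. The point concerns the randomisation stratum only, not adjustment for prognostic covariates.

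**Working it through.** The article gives no figure on this point to reproduce: no site rates, no site sizes and no design effect.

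**Inputs from the article.** Four sites, 1:1 allocation blocked within site, two-sided 0.05, 240 patients, 10% dropout, and cited recurrence of 26.6% to 51.6% across published studies (Discussion).

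**Assumptions.** Four sites of equal size, exact balance within site, and the site recurrence rates shown below.

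**Step 1: variance.** With n per arm and site rates p_s, the true variance of the difference under the null is (2/n) × mean[p_s(1−p_s)]. The unstratified chi-square uses (2/n) × p̄(1−p̄), where p̄ is the mean rate. Since p̄(1−p̄) = mean[p_s(1−p_s)] + variance of the p_s, the second is never smaller. Let r = mean[p_s(1−p_s)] / [p̄(1−p̄)]. The standard error is too large by a factor 1/√r, and the asymptotic type I error is 2 × (1 − Φ(1.96/√r)).

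**Step 2: numbers.** For sites spread over the cited range (26.6, 35, 43, 51.6%):
- mean[p_s(1−p_s)] = (0.1952 + 0.2275 + 0.2451 + 0.2497)/4 = 0.2294
- p̄ = 0.3905, so p̄(1−p̄) = 0.2380
- r = 0.2294/0.2380 = 0.964, 1/√r = 1.019, and the type I error is 4.6%

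For 15, 30, 45, 60%: r = 0.20625/0.234375 = 0.880, 1/√r = 1.066, and the type I error is 3.7%.

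| Assumed site rates (%) | r | SE too large by | Asymptotic type I error |
|---|---|---|---|
| 40 at every site | 1.000 | 0% | 5.0% |
| 30, 36, 44, 50 | 0.976 | 1.2% | 4.7% |
| 26.6, 35, 43, 51.6 | 0.964 | 1.9% | 4.6% |
| 25, 35, 45, 55 | 0.948 | 2.7% | 4.4% |
| 20, 33, 47, 60 | 0.907 | 5.0% | 4.0% |
| 15, 30, 45, 60 | 0.880 | 6.6% | 3.7% |

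**Step 3: simulation** (200,000 trials per scenario, no continuity correction, unstratified chi-square against site-stratified CMH).

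With 216 evaluable (240 × 0.9 = 4 sites × 2 arms × 27) and an assumed odds ratio of 0.5:

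| Placebo rates by site (%) | Type I error, plain / CMH | Power, plain / CMH |
|---|---|---|
| 40 at every site | 4.9% / 4.9% | 66.1% / 65.8% |
| 25 to 55 | 4.3% / 5.1% | 62.5% / 63.7% |
| 15 to 60 | 3.8% / 5.0% | 55.6% / 59.9% |

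With all 240 analysed and an assumed 18-point reduction:

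| Placebo rates by site (%) | Type I error, plain / CMH | Power, plain / CMH |
|---|---|---|
| 40 at every site | 5.3% / 5.1% | 86.0% / 86.0% |
| 30 to 50 | 5.0% / 5.2% | 86.3% / 87.0% |
| 26.6 to 51.6 | 4.8% / 5.0% | 87.2% / 88.2% |
| 20 to 60 | 4.2% / 4.9% | 87.4% / 89.8% |

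The power levels depend on the assumed effects and are not estimates of this trial's power; only the differences between the two tests matter here. At N = 240 and the 26.6–51.6% spread, the gain is 1.0 point for the 18-point reduction and about 1.4 points for an odds ratio of 0.5.

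**The case against.** The strongest objection is that nothing shows that the sites differ. The four hospitals are affiliated with one university, apply the same entry criteria (including a bowel-preparation score) and follow one endoscopy guideline. The wider spreads in the tables go beyond the whole range that the article cites across separate studies. Even if four hospitals filled that range, about 1 power point is lost. With all 240 patients analysed, as the intention-to-treat statement implies, the discrete chi-square runs slightly above its asymptotic level: 5.0% at a 30–50% spread and 4.8–4.9% at 26.6–51.6%. All of this stands, and it is why the point is conditional and small.

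A second objection is that the CMH test is itself a chi-square test, that site is not shown to be excluded from the logistic model, and that a fuller analysis plan may name the stratum. This stands in part. But the article does name the test for the primary comparison. On a plain reading that test is unstratified, so the wording at least needs clarifying.

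Two stronger readings are tempting. A reader might infer that the trial's true type I error is below 5%. The article does not support that. The shortfall needs site differences that it does not report, and it concerns one final test. The article also plans an interim analysis at 50% of the sample without stating its purpose or a boundary. If that look tested efficacy at 0.05, two looks would give about 8.3% with no site effect and 7.7% at the 26.6–51.6% spread. A reader might also infer that the p-value is invalid because it does not mirror the randomisation. The error is on the conservative side, so a significant result would remain credible.

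**Conclusion.** The mismatch between a site-stratified allocation and a recurrence test with no site stratum is real on the text. Its consequence is a conditional loss of efficiency: none if the sites are alike, about 1 power point with an asymptotic type I error of about 4.6% if they span 26.6–51.6%, and about 4 points with an error of about 3.7–3.8% only at a 15–60% spread. These sizes rest on assumed site rates, equal site sizes, exact balance within site and illustrative treatment effects. Across the scenarios simulated, CMH stays close to 5%. When the sites do not differ its power is the same to within 0.3 points, so stratifying costs practically nothing. This is a minor improvement worth making, not a flaw that threatens the trial's conclusion.

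**What to change.** In the Statistical analysis section, state that year-1 and year-2 recurrence will be compared with a Cochran-Mantel-Haenszel test stratified by recruiting site. Report the Mantel-Haenszel common risk difference or risk ratio with its 95% confidence interval. Keep the unstratified chi-square as a sensitivity analysis. If a stratified chi-square was meant all along, saying so is enough for the test itself.

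The cost is a few sentences. Site is already known for every patient, and no new data or extra patients are needed. Make the change before treatment codes are opened, so that the choice between the two tests cannot depend on the results.

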### Trial status

We planed to recruit participants from January 2023 and complete the recruitment in June 2024. The follow-up will finish in September 2025. All clinical data will be locked in November 2025. This protocol was submitted before completion of recruitment.

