**FIGURE 1 F1:**
[figure not shown]
The flowchart of the trial.

This is a multicenter, double-blinded, randomized controlled trial (RCT) of two parallel groups. A total of 240 cases will be recruited by recruitment advertisements and introductions from clinicians at outpatient or inpatient departments. Patients who meet the inclusion criteria will be informed of the possibility of participating in this study at the outpatient clinic or at admission. A face-to-face interview will be arranged to inform the patients about the purpose, interventions, examinations and follow-up procedures of this study. After informed consent acquisition, patients will be randomized to the SJZD group or placebo group at a ratio of 1:1. An intervention phase with a 12-month treatment with SJZD granules or placebo will be implemented for recruited patients. Endoscopy will be conducted at the end of the intervention phase and 1 year later. The duration of follow-up is 24 months with 5 visits, and the schedule details are listed in Table 2.

**TABLE 2 T2:** Schedule of trial.

	Period					
Study phase	Enrollment	Visit 1	Visit 2	Visit 3	Visit 4	Visit 5
		3 months of interventions	6 months of interventions	9 months of interventions	12 months of interventions	The second year after intervention
Informed consent form	**√**					
Demographic information	**√**					
Inclusion and exclusion criteria	**√**					
General information	**√**					
Vital signs	**√**	**√**	**√**	**√**	**√**	**√**
Spleen deficiency rating scale	**√**	√	√	√	√	√
Endoscopy	**√**				√	√
Histological tests*	**√**				√	√
Routine blood tests	**√**	√	√	√	√	
Routine urine test	**√**	√	√	√	√	
Routine stool test	**√**	√	√	√	√	
Liver function	**√**	√	√	√	√	
Renal function	**√**	√	√	√	√	
Electrocardiograph	**√**	√	√	√	√	
Serum and stool samples collections	**√**				√	√
Adenomatous tissue collections*	**√**				√	√
Adverse events		√	√	√	√	√
Release drugs/placebo	**√**	√	√	√		
Retrieve empty packages			√	√	√	
Drug combination	**√**	√	√	√	√	√

Notes: Patients who are detected to find recurrence of colorectal adenoma and meet the criteria of resection are undergone endoscopy. Adenomatous tissue will be collected according to the relevant regulations and histology will be confirmed by pathological experts.

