### Interventions

#### Drug intervention

The intervention phase will last 12 months. Both SJZD and placebo are designed as granules with the same weight (1.77g/pack) and packaging. The appearance, texture, smell and taste of placebo granules are the same as SJZD granules but without any therapeutic effect. The granules in one package are dissolved in 200 mL of hot water. Patients are asked to take two packages orally two separate times in 1 day (3.54 g/day). There is no reduction or escalation of drug dose and frequency. SJZD and placebo are provided by Sichuan Neo-green Pharmaceutical Technology Development Co., Ltd. (Sichuan, China). The ingredients of placebo include one-tenth dose of SJZD (Radix ginseng, Rhizoma Atractylodis macrocephalae, Poria and Radix Glycyrrhizae Preparata) and maltodextrin. All the processing and preparation of medications and placebo are qualified. For participants who have severe adverse events (AEs) relevant to this trial, post-trial care will be arranged, and additional pecuniary compensation will be given. For participants who have adverse reactions not related to the drug in this trial, the relevant medical interventions will be implemented based on the comprehensive information of patients, including previous medical histories, symptoms and signs, laboratory, imaging and other examination results.

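### Follow-up is dated to end in September 2025, nine months before the last recruited patient is due for the month-24 endoscopy

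*Protocol article*

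**What the plan says.** The Trial status section gives the calendar. Its sentence on recruitment reads "We planed to recruit participants from January 2023 and complete the recruitment in June 2024". On closing the observation period it says "The follow-up will finish in September 2025". For the database it adds "All clinical data will be locked in November 2025".

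The schedule per patient stands elsewhere in the article:

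- Drug intervention: "The intervention phase will last 12 months".
- Study design and setting, on the two follow-up examinations: "Endoscopy will be conducted at the end of the intervention phase and 1 year later". The same section, on the length of observation: "The duration of follow-up is 24 months with 5 visits".
- Outcomes: the first secondary outcome is "the recurrence rate of CRA at the second year post-polypectomy". The second, pathological type, draws on both follow-up endoscopies.
- Table 2: visits 1 to 4 fall at months 3, 6, 9 and 12 of treatment, and visit 5, which includes an endoscopy, is headed "The second year after intervention".

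The Abstract and the limitations paragraph of the Discussion also give 24 months of follow-up. The inclusion criteria place the resection no more than two weeks before recruitment, so the clock from polypectomy and the clock from enrolment nearly coincide. The Statistical analysis section fills missing data by last observation carried forward (LOCF). No section sets an administrative cut-off, limits the year-2 endoscopy to early enrollees, or ties September 2025 to a primary analysis only.

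**The concern.** The calendar and the schedule per patient cannot both be followed. If follow-up closes on the stated date, patients recruited in the later part of the window will never have been due for visit 5 when it closes. Their year-2 endoscopy would be missing because of the plan, not because of anything the patient did.

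The year-2 recurrence outcome, the year-2 part of the pathology outcome and the other visit 5 data are at stake. Under the LOCF rule, the year-2 value of a patient cut off in this way would be the month-12 result. The Discussion itself reports that recurrence rises with longer follow-up. A patient free of adenoma at month 12 would be counted as free at month 24 without having been examined, which tends to understate year-2 recurrence and pulls the year-2 comparison towards the year-1 comparison.

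**Working it through.** **Inputs.** Recruitment January 2023 to June 2024, end of follow-up September 2025 and lock November 2025 (Trial status). 24 months per patient with endoscopy at months 12 and 24 (Study design and setting; Drug intervention). N = 240 (Study design and setting). Dropout allowance 10% per group (Sample size). The accrual pattern is not given and is an assumption below.

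**Can the stated date be reproduced?** End of follow-up = last enrolment + follow-up per patient.

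- June 2024 + 12 months = June 2025
- June 2024 + 24 months = June 2026
- September 2025 = June 2024 + 15 months

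No visit in Table 2 falls at month 15, so the stated date is not reproduced. June 2026 is 9 months after September 2025 and 7 months after November 2025. The date would fit 24 months of follow-up only if recruitment had ended by about September 2023.

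**Who can complete visit 5?** The latest enrolment that reaches month 24 in time is September 2025 − 24 months = September 2023. January to September 2023 is 9 of the 18 recruitment months.

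**Share cut off under even accrual.** 1 − 9/18 = 50%, or 0.50 × 240 = 120 patients. The figure moves with how the dates are read:

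| Reading (even accrual) | Cut off | Of 240 |
|---|---|---|
| Follow-up ends 1 September 2025 | 55% | 133 |
| Follow-up ends 30 September 2025 | 50% | 120 |
| Same, 24 months counted from a resection two weeks before enrolment | 47.5% | 114 |
| Endoscopies continue to the lock, 30 November 2025 (1 − 11/18) | 39% | 93 |

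**Share cut off under other accrual shapes** (follow-up ends 30 September 2025, half of the window elapsed):

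- Linearly rising accrual: 1 − (9/18)² = 75%.
- Six-month linear ramp-up, then constant: total 0.5 × 6 + 12 = 15 units, of which 0.5 × 6 + 3 = 6 are in time, so 1 − 6/15 = 60%.
- Linearly falling accrual: (1 − 9/18)² = 25%.

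The two lenient assumptions together, falling accrual and visits up to the lock, still give (7/18)² = 15%.

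**Primary outcome.** The last patient reaches month 12 in June 2025, before September 2025. No patient is cut off.

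**The case against.** The strongest defence is that the dates stand in a prospective status note, while every design section consistently gives 24 months. On that view this is a slip in one date, and the primary outcome does not depend on it. Much of this stands. The month-12 endoscopy is reachable for everyone. Loss by enrolment date should also be roughly balanced between arms under blocked 1:1 randomization stratified by site. But the data lock is set to match the wrong date, and a trial closed on these dates would truncate a named secondary outcome.

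A second defence is that the LOCF sentence is generic and that an analysis plan, not shown here, may treat visits never due separately. That is possible, so the carry-forward consequence is conditional on the rule as written. The Outcomes section also does not say whether year-2 recurrence is cumulative. If it is, a patient who recurred by month 12 is already counted correctly, and the error lies with those still free at month 12. No analysis plan, however, can bring a June 2026 visit before September 2025.

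A reader might infer more than the documents support:

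- **That no patient can reach visit 5.** This takes the Table 2 heading to mean 24 months after treatment ends, 36 months in all, so that the first visit 5 would fall in January 2026. The text rules this out: the second endoscopy is one year after the intervention ends, the 24 months contain all five visits including the four during treatment, and the outcome is timed from polypectomy. The heading is loose, but the text settles it at month 24.
- **That half of the patients are lost as a matter of fact.** That holds only under even accrual.
- **That the year-2 result would largely repeat year 1.** Carry-forward affects only the patients cut off. The others would have real month-24 data.

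**Conclusion.** The dates are wrong as written. With recruitment to June 2024 and 24 months per patient, follow-up cannot finish before June 2026. This follows from the article's own figures and needs no assumption.

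The size does need one. About 50% of patients (120 of 240) would miss the year-2 endoscopy under even accrual, about 25% to 75% across the accrual shapes tried, and 39% under even accrual if visits run to the lock. All of these exceed the 10% allowed for dropout.

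The harm is confined to the year-2 recurrence outcome, the year-2 part of the pathology outcome and other visit 5 data. It is a loss of precision and, if month-12 values are carried forward, a tendency to understate year-2 recurrence. The correction should be made before follow-up closes, because year-2 endoscopies not done on time cannot be recovered afterwards.

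**What to change.** Reconcile Trial status with Study design and setting and with Outcomes. Move the end of follow-up to June 2026 or later, plus the visit window, and place the data lock after it. Release of the treatment codes is tied to closure of follow-up, so it should move with the new date. Label visit 5 in Table 2 as month 24 (second year after polypectomy), so that the table and text agree.

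If September 2025 must stand, state that the year-2 outcome is estimated only in patients enrolled by about September 2023, and do not carry month-12 results forward for visits that were never due.

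The first option costs an amendment of two dates and one table heading, and about nine more months of visits that the protocol already promises. The second costs no time, but gives up year-2 information on every patient enrolled after about September 2023.
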